### Sample size

In a preliminary analysis of observational data, we observed that the proportion of days spent in an institution was 0.04 (SD = 0.12) for Meals on Wheels clients in the 6 months after receiving meals compared to 0.07 (SD = 0.19) among similar individuals that were not receiving meals. Because we are comparing two modes of meal delivery, we assume that the difference in proportions between the two modes of meal delivery is 0.02. Using a two-sample *t*-test, and assuming a 1:1 randomization, two-tailed test, and α = 0.05, we need a sample size of 1984 participants, 992 in each arm, to detect a 2% difference in the proportion of days spent in institutional settings to achieve 80% power. In the rare case we have difficulty deterministically linking participant data to their CMS data, we will use probabilistic linking techniques [22, 31]. Given that in prior research we have been able to identify 1-to-1 matches for 87% of Meals on Wheels clients using probabilistic methods, we are targeting enrollment of 2300 participants to ensure that we will have adequate sample size if we have unexpected linking challenges.

We have found during the study that some participants live in the same household with another participant. In situations where participants are living together, we are randomizing the entire household to the same meal assignment. We estimated the impacts on power for scenarios spanning from 10% of participants living in shared households to 30% using a sample size formula for cluster randomized trials [32]. With 1984 participants, only at the highest level of shared household proportions (30%) with highly correlated outcomes (0.1 ICC) did the power decrease from 0.80 to 0.79. We are monitoring the frequency of shared households and will adjust our sample size, as necessary.

### Statistical methods

#### Primary outcome analysis

Our primary analysis is an intention-to-treat analysis, meaning that we will assess outcomes for all participants assigned to each group regardless of how long they continue to receive meals. In randomized experiments, the distribution of all the covariates should be similar on average. However, because there are many covariates (e.g., age, education), one may expect that some will suffer from slight imbalances. Using the baseline survey data and participants’ prior Medicare claims, we will test for balance in these covariates between the two arms by comparing means and proportions. To address any minor imbalances and to obtain a more efficient estimate, we will use regression adjustments to estimate the marginal average treatment effect. Because outcomes of individuals within the same household may be correlated, we will use a hierarchical model to adjust for these correlations. Standard errors will be obtained using the bootstrap procedure.

#### Heterogeneity in treatment effects

We hypothesize that the treatment effect will differ among preference groups, with participants who receive a meal delivery method that is concordant with their preferences having better outcomes than those who do not receive a meal delivery method concordant with their preference. We will therefore conduct stratified analyses by each of the four preference groups: (1) preferred and received daily meals, (2) preferred daily meals and received drop-shipped meals, (3) preferred and received drop-shipped meals, (4) preferred drop-shipped meals and received daily meals. We will compare the ratio of days in institutional settings among the intervention groups and examine if they are significantly different across subgroups. To adjust for multiple comparisons, we will perform Bonferroni correction [33].

Based on research examining factors predicting institutionalization [34, 35], we expect that the treatment effect will differ between participants’ living alone from those living with others. We will conduct subgroup analyses to determine if differences in the intervention effect differs between the two living arrangement groups. We hypothesize that the difference in the primary and secondary outcomes between the two arms will be greater for participants who live alone than those who live with others. To test for the significance of heterogeneity of treatment effect by living arrangement, we will use the common *t*-distribution [36].

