**Methods:**

With extensive stakeholder input, we designed and implemented a pragmatic randomized comparative effectiveness study in which we will enroll 2300 older adults on waiting lists at home-delivered meals programs across the country and randomize them to receive for 6 months, either (1) weekday lunchtime meals delivered by a local volunteer or driver who also provides socialization and wellness checks or (2) biweekly delivery of 10 frozen meals to participants’ homes. Participant data will be combined with Centers for Medicare and Medicaid Services (CMS) data to calculate post-randomization institutional vs. community days. Baseline and 3-month surveys will evaluate secondary outcomes (e.g., food insecurity, loneliness, quality of life) and exploratory outcomes (e.g., nutritional risk). To examine heterogeneity of treatment effects, we will test for interactions between the two types of meal delivery and participants’ preferred mode of meal delivery as well as participants’ living arrangements.

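### Single-step Bonferroni for the preference-group comparisons is valid, but Holm's step-down gives the same family-wise protection and more power wherever two or more hypotheses are tested

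*Protocol article*

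**What the plan says.** Under Heterogeneity in treatment effects, the Protocol article forms four groups from preferred mode crossed with mode received: "We will therefore conduct stratified analyses by each of the four preference groups". The outcome is the ratio of institutional days. The inference announced is significance testing, to "examine if they are significantly different across subgroups", followed by "To adjust for multiple comparisons, we will perform Bonferroni correction". That section does not state how many comparisons make up the family, and it mentions no simultaneous confidence intervals. The Methods paragraph of the abstract puts the same question in a different form: "we will test for interactions between the two types of meal delivery and participants’ preferred mode of meal delivery".

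The Sample size section covers the overall comparison of arms only, "assuming a 1:1 randomization, two-tailed test, and α = 0.05", with 992 per arm for 80% power. It gives no power for the preference comparisons.

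**The concern.** Bonferroni tests every hypothesis at 0.05/m. Holm starts at the same threshold for the smallest p-value and then relaxes it to 0.05/(m−1), 0.05/(m−2) and so on, for as long as it keeps rejecting. It needs no assumption about dependence between tests, just as Bonferroni needs none. For pure significance testing of two or more hypotheses, Bonferroni is therefore the less powerful of two procedures with the same family-wise guarantee.

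The difference is relevant here for two reasons. First, the stated hypothesis is that concordance helps: daily delivery for those who prefer it, and drop-shipped meals for those who prefer those. Supporting it in full takes a rejection in each stratum, and second rejections are where Holm gains. Second, each comparison uses a fraction of a sample sized for the overall contrast, so power is already limited.

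**Working it through.** **Inputs from the article (Sample size).** Two-sided α = 0.05; difference between modes, "we assume that the difference in proportions between the two modes of meal delivery is 0.02"; SDs from "was 0.04 (SD = 0.12) for Meals on Wheels clients in the 6 months after receiving meals" and "compared to 0.07 (SD = 0.19) among similar individuals that were not receiving meals"; 1984 analysed.

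**Reproducing the stated size.** Pooled SD = √[(0.12² + 0.19²)/2] = 0.159. Per arm, n = 2 × (1.960 + 0.842)² × 0.159² / 0.02² ≈ 991 by the normal approximation; the exact t-test gives 991.9, so 992. The stated figure reproduces. SD 0.12 alone gives 566 and SD 0.19 alone gives 1417, so 0.159 is the SD to carry forward.

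**Assumptions that the article does not supply.** Preference split 60/40, giving 595 per arm in the larger stratum and 397 per arm in the smaller. The concordance effect is taken as 0.02 (the plan's own difference between modes) or 0.03. The family is one, two or six tests.

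**One interaction test (m = 1).** Both methods test at 0.05. Gain: zero.

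**Two within-stratum arm differences (m = 2).** The standard error is 0.159 × √(2/n): 0.00921 and 0.01128. Let B be the power of a test at 0.025 and U its power at 0.05. The strata are independent, so Holm's power for stratum 1 is B₁ + (U₁ − B₁) × B₂, and likewise for stratum 2. Power to reject both is B₁B₂ under Bonferroni and B₁U₂ + U₁B₂ − B₁B₂ under Holm.

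At an effect of 0.02, B = 0.472 and 0.320, and U = 0.584 and 0.426:
- Larger stratum: 0.472 + 0.112 × 0.320 = 0.508.
- Smaller stratum: 0.320 + 0.106 × 0.472 = 0.370.
- Both: 0.472 × 0.320 = 0.151 under Bonferroni; 0.201 + 0.187 − 0.151 = 0.237 under Holm.
- At least one: 1 − 0.528 × 0.680 = 0.641 under either method.

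At an effect of 0.03, B = 0.845 and 0.662, and U = 0.903 and 0.758. The same formulas give 0.845 to 0.883, 0.662 to 0.743, and both 0.559 to 0.679.

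**Six pairwise tests (m = 6).** Simulated group means, 400,000 replicates, z-tests, group sizes 595/595/397/397. Groups 1 and 3 are concordant, 2 and 4 discordant.

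| Contrast | 0.02: Bonferroni | 0.02: Holm | 0.03: Bonferroni | 0.03: Holm |
|---|---|---|---|---|
| 1 v 2 | 0.32 | 0.34 | 0.73 | 0.77 |
| 1 v 4 | 0.24 | 0.27 | 0.61 | 0.66 |
| 3 v 4 | 0.19 | 0.22 | 0.51 | 0.57 |
| At least one | 0.56 | 0.56 | 0.92 | 0.92 |

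**Error control.** Holm retained nothing that Bonferroni rejected in any replicate. With all six hypotheses null, the family-wise error was about 0.042 for both. With a 0.03 effect it was 0.016 for Bonferroni and about 0.029 for Holm, both below 0.05.

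**Other splits (m = 2, effect 0.02 in both strata).** Power to reject both goes from 0.16 to 0.25 at 50/50, from 0.13 to 0.21 at 70/30, and from 0.08 to 0.13 at 85/15.

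**The case against.** A reader might infer that the plan makes an error here, or that it gives power away for nothing. The article does not support either reading. Bonferroni is valid and conservative, inflates no error rate, makes no stated figure wrong and leaves the primary comparison and its 80% power untouched.

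Something is also traded. Bonferroni bounds the expected number of false rejections at 0.05 as well as the family-wise error, and its actual error rate is lower when some hypotheses are false. It also gives simultaneous intervals that agree with its tests. The first two differences are small, and Holm stays within 0.05. The third carries limited weight because the section announces only significance testing, although it does not rule out intervals.

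Nor may a reader infer that Bonferroni makes the trial more likely to miss a preference effect altogether. Holm's first step is Bonferroni, so the chance of at least one rejection is the same.

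The size of the gain rests on inputs that the article does not give. A 0.03 effect is 1.5 times the plan's assumed difference between modes and equals the whole observed gap between meals and no meals (0.07 − 0.04). Six pairwise tests include two contrasts, concordant with concordant and discordant with discordant, that the hypothesis does not need. If the abstract's interaction is a single test, there is no gain. All of this stands, and it is why the result is given as a range starting at zero.

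Finally, the family may be set out in an analysis plan that is not shown. Its size is not raised here as a gap. The point concerns only the method that the article names.

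**Conclusion.** The point holds as an optional efficiency improvement of low severity. For any family of two or more preference tests, Holm gives the same family-wise guarantee and rejects at least as much. Under SD 0.159, 1984 analysed and a 60/40 split, the gain per contrast is:
- zero with a single interaction test;
- about 2 to 3 points (effect 0.02) or 4 to 6 points (effect 0.03) with six pairwise tests;
- about 4 to 5 points (0.02) or 4 to 8 points (0.03) with two within-stratum tests.

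The more relevant gain is in establishing the hypothesis in both strata: 0.15 to 0.24 at an effect of 0.02 with two tests. Even then power is low, so Holm does not make these analyses well powered.

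**What to change.** In Heterogeneity in treatment effects, replace 'Bonferroni correction' by 'Holm step-down adjustment at family-wise 0.05', applied to the preference contrasts actually tested, and do so before outcome data are analysed. The cost is one phrase in the plan and one option in the code, with no change to sample size or data collection. If simultaneous confidence intervals are also reported, Bonferroni limits can be kept for them, with a note that a Holm rejection may occasionally accompany an interval that includes zero.

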#### Supplementary analyses

Because we are interested in the effect of the intervention and not only the effect of being randomized to receive the intervention, we will conduct a supplementary compliance analysis [37, 38]. We will examine the effect of the intervention only among participants who received the meals for at least 4 weeks in both arms and for participants who received meals for at least 3 months (consistent with the timeline for our secondary outcome measures). To do so, we will use the principal stratification framework, which has been proposed as a plausible solution to address non-compliance in randomized trials [39]. We will use the Bayesian framework to identify compliers [37, 40]; this will allow us to examine the sensitivity of our results to commonly-used identifying assumptions (e.g., monotonicity, exclusion restriction). With our modeling assumptions, we can identify characteristics that are indicative of compliance with assigned intervention, which would allow for better tailoring of meals in the future.

We do not expect that the different interventions will affect mortality. However, we will monitor whether there is a differential difference in mortality, by arm. If one is observed, as a supplementary analysis, we will use principal stratification analysis to account for differential mortality [41]. We will also conduct exploratory analyses to determine if the treatment effects vary by comorbidities ascertained from CMS data, as well as by baseline food insecurity status and baseline loneliness/social isolation.

#### Secondary and exploratory outcomes analysis

For our secondary outcomes, we will examine claims data for the 3-month institutional care use measure and conduct pre- and post-intervention telephone surveys for the patient-reported secondary outcomes. Pre- and post- loneliness, food insecurity, and health-related quality of life measures will be directly compared. For our exploratory outcome, nutritional risk, we will directly compare pre- and post-Dietary Screening Tool scores for the sub-sample of 600 randomly selected participants. For the exploratory outcomes requested by our advisory panels (emergency room visits, hospitalizations, and avoidable hospitalizations), we will use CMS data and compare the rates and times to events between the two arms.

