An important aspect of addressing food insecurity among homebound older adults is doing so in a way that aligns with their preferences. However, there is limited evidence about which mode of home-delivered meals older adults prefer. Many healthcare entities and community-based organizations strive for person-centered care, but there is little evidence to guide them on what mode of meal delivery older adults prefer or how receiving meals that older adults prefer may affect satisfaction and ultimately outcomes. Therefore, decision-makers have little evidence on either (a) which mode of delivery is more effective in reducing costly healthcare utilization and improving older adults’ quality of life and (b) how the effect of meal delivery on health and utilization outcomes may vary as a function of older adults’ meal delivery preferences.

To address these gaps in knowledge, we are conducting a multi-site, randomized pragmatic comparative effectiveness study with two parallel arms (the two modes of meal delivery) and a primary endpoint of institutional healthcare use in the 6 months after enrollment. The objective of this paper is to describe our protocol for the trial and present how it was shaped by stakeholder input (e.g., older adults receiving meals, meal providers, healthcare representatives). We specifically highlight the regulatory and resource challenges in responding to stakeholder input when designing and implementing this study.

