### Data collection

Survey data are being collected for all participants pre-intervention (baseline) and 3 months later (follow-up). Survey questions include items to assess demographics, preference for daily or drop-shipped meals, and health and well-being (e.g., food insecurity, health-related quality of life). To assess our exploratory outcome, nutritional risk (described below), we are conducting a longer survey that includes the Dietary Screening Tool with 600 randomly-selected participants. Additionally, we are conducting semi-structured telephone interviews with approximately 50 participants two months after they begin receiving services to collect information about their experiences receiving meals, how these services may have impacted their lives, and their satisfaction with these services. We are purposefully selecting participants for the semi-structured interviews across programs, treatment arm, preference, and living situation. A member of the research team contacts a participant selected for a qualitative interview and invites them to participate. These interviews take approximately 30–45 min to complete. Additional data sources include participant and service data from participating Meals on Wheels programs and claims, assessment, and enrollment files from the Centers for Medicare and Medicaid Services (CMS). We obtained a HIPAA waiver of authorization to use the CMS data. See appendix for information on data management and maintaining confidentiality.

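### The stated analysis of the survey outcomes and Dietary Screening Tool is a pre-versus-post comparison that names no arm contrast, so read literally it does not estimate the difference between delivery modes

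*Protocol article*

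**What the plan says.** All of this is in the protocol article.

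- **Secondary and exploratory outcomes analysis**, on the patient-reported secondary outcomes: "Pre- and post- loneliness, food insecurity, and health-related quality of life measures will be directly compared".
- The same section, on nutritional risk: "we will directly compare pre- and post-Dietary Screening Tool scores for the sub-sample of 600 randomly selected participants".
- The same section, on emergency visits and hospitalisations: "we will use CMS data and compare the rates and times to events between the two arms".
- **Primary outcome analysis** gives a between-arm estimate, under that heading only: "we will use regression adjustments to estimate the marginal average treatment effect".
- **Heterogeneity in treatment effects** mentions an arm difference in secondary outcomes, as a living-arrangement hypothesis: "We hypothesize that the difference in the primary and secondary outcomes between the two arms will be greater for participants who live alone".
- **Introduction**, on the design: "randomized pragmatic comparative effectiveness study with two parallel arms (the two modes of meal delivery".
- **Data collection**, on timing: "Survey data are being collected for all participants pre-intervention (baseline) and 3 months later (follow-up".

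**The concern.** The trial asks whether one delivery mode does better than the other. Participants are recruited from waiting lists and both arms are assigned meals. A pre-post comparison therefore picks up whatever both arms share: the effect of getting meals at all, the passage of time, and possibly regression to the mean. None of these separates daily from drop-shipped delivery.

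If the sentences were followed as written, two errors become likely. A pooled pre-post result could be strongly significant with no difference between modes. Or separate within-arm tests could be significant in one arm and not the other, and be read as a difference. At stake are loneliness, food insecurity, health-related quality of life and nutritional risk. The background section cites prior evidence that loneliness may differ by delivery mode, so the unstated contrast is one of scientific interest.

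**Working it through.** **1. What the text fixes, outcome by outcome**

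| Outcome | Contrast stated for the overall analysis | Arm contrast elsewhere |
|---|---|---|
| 6-month institutional ratio (primary) | Regression-adjusted average treatment effect | Not needed |
| 3-month institutional ratio (secondary) | Claims data to be examined; arms not named | Defined like the primary outcome in Table 1 |
| Food insecurity, loneliness, quality of life (secondary) | Pre against post; arms not named | Only in the living-arrangement hypothesis |
| Dietary Screening Tool (exploratory) | Pre against post; arms not named | None beyond the two-arm design |
| Emergency visits, hospitalisations (exploratory) | Rates and times to event, between the arms | Not needed |

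**2. The plan's own figures.** The article gives no sample size, SD or power for the survey measures, so there is nothing to reproduce for them. The primary figure does reproduce. With SD = √((0.12² + 0.19²)/2) = 0.1589 and difference 0.02, a two-sided 5% test with 80% power needs 2 × ((1.960 + 0.842) × 0.1589/0.02)² ≈ 991 per arm, or 992 with the t distribution, as stated. This point does not touch it.

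**3. What a literal pre-post test would do.** Assumptions: 300 per arm (the 600 of the dietary sub-sample), SD 1 at both times, correlation r = 0.5, two-sided 5%, complete follow-up. The SD of the change is √(2(1 − r)) = 1. The simulations used 2,000 runs per scenario.

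- *Both arms improve by 0.2 SD; true arm difference 0.* Pooled pre-post: z = 0.2 × √600 = 4.9. It was significant in over 99% of runs; the baseline-adjusted arm comparison (ANCOVA) in about 5%.
- *Both arms improve by 0.1 SD; true arm difference 0.* Within one arm: z = 0.1 × √300 = 1.73, power about 0.41. The chance that exactly one arm is significant is 2 × 0.41 × 0.59 ≈ 0.48; simulation gave 47%.
- *Arms move 0.1 SD in opposite directions; true arm difference 0.2 SD.* The pooled mean change is 0, so pre-post rejects in about 5%. ANCOVA: z = 0.2/√(2 × 0.75/300) = 2.83, power about 0.81; simulation gave 80%.

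The pre-post result can thus be near-certain when the arm difference is zero, and at its false-positive rate when the difference is real.

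**4. If the intention is change from baseline compared between arms.** That is valid under randomisation but less precise. With a common SD, the variance is proportional to 2(1 − r) for the change score and 1 − r² for ANCOVA. The ratio is (1 − r²)/(2(1 − r)) = (1 + r)/2: 0.70 at r = 0.4, 0.75 at r = 0.5 and 0.85 at r = 0.7. Baseline adjustment therefore cuts the variance by 15 to 30% over that assumed range. This is an efficiency gain and does not measure the defect in step 3.

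**The case against.** The strongest reply is that these are elliptical sentences in a condensed article, not a decision to abandon the arm comparison. Several places support this. The heterogeneity section presupposes an arm difference in secondary outcomes. Table 1 lists the survey outcomes at 3 months, not as change. Follow-up interviewers are blinded to condition, which mainly serves a between-arm comparison. The same section also omits the arms for the 3-month institutional ratio, which is plainly comparative. Naming the arms for the event outcomes alone therefore does not prove that they were dropped elsewhere.

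Most of this stands. A reader might infer that the trial has settled on a pre-post analysis with no arm comparison of the survey outcomes; the documents do not support that. A reader might also infer that baseline scores are excluded as covariates. The article is silent there, and silence on a covariate list is normal in an article. It would also be too strong to say that everyone goes from no meals to meals, since participants may decline or stop them. Finally, the simulated pooled and separate tests are possible readings; the article specifies neither.

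What does not stand is the view that nothing needs correcting. This is not mere silence: the article states a contrast for these measures, and it is the wrong one for the question. The subgroup hypothesis presupposes an arm effect without giving its overall analysis, and it does not reach the Dietary Screening Tool.

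**Conclusion.** The point holds as a should-fix for three secondary outcomes and one exploratory outcome. The stated comparison, taken literally, does not estimate or test daily against drop-shipped delivery, and the article never states the overall between-arm analysis of these measures. An arm comparison is probably intended for the secondary outcomes, so this may be poor wording rather than a wrong plan.

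The rejection rates in the working show the direction and seriousness of a literal reading. They rest on assumed SD, correlation and retention, not on trial data.

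**What to change.** State in the protocol or analysis plan that each 3-month survey score, including the Dietary Screening Tool score in its sub-sample, is compared between the randomised arms. Adjust for the baseline value of the same measure and for the randomisation strata (program, preference, living arrangement), and allow for household clustering as is already planned for the primary outcome. Report the adjusted arm difference with its 95% CI. Keep within-arm pre-post change as description only.

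The cost is wording and a little analysis. The baseline and 3-month scores and the strata are already being collected, and neither the sample size nor the primary analysis changes. The wording should be settled before outcome data are analysed.
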